#### Follow-up

In order to assess the primary outcomes—how often they used sunscreen and how many times they got sunburns in the prior month—subjects will be mailed a post-intervention survey in the fall. Subjects will receive $10 for each pre- and post-intervention survey.

### Description of sun protection interventions

#### Education only

Since studies have shown that increased knowledge regarding sunscreen use is efficacious in increasing awareness and fostering preventive health behaviors [33-36], a 30 minute power point presentation will be offered to Operating Engineers during their annual safety trainings. The content of the 30-minute didactic power point presentation was gathered from various sources including published articles, guidelines from the U.S. Food and Drug Administration (USFDA), the U.S. Preventive Services Task Force (USPSTF), and the American Academy of Dermatology (AAD). The content will include background information on the current use of sun protection among Local 324 members taken from a previous survey of this population [23], information on incidence and prevalence of skin cancer especially among outdoor workers, and the types of skin cancers and skin cancer risk. The content will also include methods to prevent sun burning including choosing from different products and reading Sun Protection Factor (SPF) labels recommended by the USFDA (2012) and USPSTF (2012), truths and myths about SPF [37], correct application of sunscreen, and other sun protection behaviors such as wearing hats, sunglasses, using shade, etc.

Adopting or tailoring information to address the needs of a specific population is important in order to overcome the perceived susceptibility, perceived severity, perceived barriers and increase the perceived benefits [29,36,38-41]. To make the presentation personal to Operating Engineers, pictures of Operating Engineers working in the sun will be scattered throughout. Visualization, such as pictures and graphs, enhances the understanding by taking the information to a more concrete level compared to verbal symbols alone [42]. Since the literature showed that pictures of skin cancer can motivate people to action [33] and inducing negative emotions can persuade people to act particularly when a solution is offered [25], pictures of skin cancer will be shown. Pictures on different SPF labels and sunscreens will be shown as well.

The second half of the session will be used for open discussion with Operating Engineers to address their perceived barriers and opinions about using sunscreen. This will allow for a greater understanding of the specific issues related to sun protection in the target population. By addressing the barriers to sun protection use and identifying strategies to overcome them, the participants are more likely to practice the desired behaviors [38-40].

#### Education and sunscreen

To reduce barriers to obtaining sunscreen and serve as cues to action, in addition to education, this group will be mailed sun screens three times over the summer, a supply of SPF30 sunscreen lotion (known to prevent sun burning and skin cancer) [43]. The mailing will consist of large bottles of sunscreen and a small bottle that can be refilled and attached to their huge key rings that hang off of their belts.

#### Education and text-message reminders

Recall of sun protection messages has been shown to be problematic [44], but the provision of text-message reminders has been found to increase adherence to sunscreen application in one study [31]. Hence, in addition to education and as cues to action, this group will receive 60 unique cellular telephone text-messages in the morning on three random days per week for the months of May, June, July, August and September. Using an internet text-messaging service, the messages will be computer generated and sent to Operating Engineers and contain information about weather conditions and various reminders (e.g., “Put on sunscreen today” or “Wow, it’s a hot one, you know what to do!”). The text message bank was developed by requesting suggestions for potential text messages from students, faculty and leadership at Operating Engineers Local 324. Since positive messages have been found to emphasize the good and appeal to the listener’s desire for good, happy emotions [45], which we want to convey during the Operating Engineers working hours, negatively oriented text messages were excluded from the message bank.

#### Education, sunscreen, and text message reminders

Just as multimodal interventions such as surgery and radiation can be used to treat skin cancer, multimodal behavioral interventions may reduce sun burning and prevent skin cancer. To determine if the combination of these interventional components results in improvements above and beyond the individual parts, both sunscreen and text messaging interventions will be provided in addition to education.

### Measures

#### Independent variables

The independent categorical variables will consist of 3 dummy variables created from the four sun treatment conditions using the education only as the reference group.

#### Dependent variables

Since self-report has been shown to be a valuable measure when skin reflectance measurement is not feasible [46], sun exposure will be assessed using two validated questions [47]. In the past summer, on the days when you were outside in the sunlight, how often did you use sun block (never, some of the time, about half the time, most of the time, always)? On average, how many times did you get a sunburn this past summer (0, 1, 2, 3, 4 or more times)?

#### Sun exposure covariates

To measure sun exposure, Operating Engineers will be asked four questions. About how many times in your life do you recall having had a sunburn severe enough to cause your skin to blister (write in number)? In general, during the summer week days, about how many hours a day are you outside between 10 am and 3 pm? In general, during the summer holidays and weekends, about how many hours a day are you outside between 10 am and 3 pm (less than an hour, 1 to 2 hours, 2 to 3 hours, 3 to 4 hours, 4–5 hours)? Which best describes how your skin generally reacts to the sun when you’re not using any sun protection (always burn-unable to tan, usually burn-then can tan if I work at it, sometimes mild burn-then tan easily, rarely burn-tan easily) [47]?

#### Health belief model covariates

The impact of the intervention on the four components of the Health Belief Model, which have been empirically supported by previous studies, will be measured with questions (rated on a 5-point scale) similar to those used in our tobacco cessation studies [48]. Perceived susceptibility will be measured by the questions: How likely do you think you are to sunburn next summer? and How likely do you think you are to develop skin cancer? Perceived severity will be measured by the questions: How bad would it be for you to get sunburned? and How bad would it be for you to get skin cancer? Perceived benefits to using sun protection will be measured by the question: How important is it that you prevent sun burning? and How important is it that you prevent skin cancer? Perceived barriers will be measured by the question: How difficult will it be to apply sun protection regularly [49,50]?

Several mediators of the Heath Promotion Model will also be measured. Self-efficacy will be measured by the question: How confident are you that you can apply sun protection regularly? Cues to action, which will vary depending on the intervention to which subjects were randomized, will be measured by the question: The educational presentation and/or mailed sunscreen and/or text message reminders increased the likelihood that I will use sunscreen.

Psychological status will be measured using the well validated Center for Epidemiologic Studies/Depressed Mood Scale (CES-D-SF) [51]. Since medical comorbidities can increase health motivation, comorbidities will be measured using a validated self-report instrument [52]. Since demographic factors may mediate sun protection behaviors, age, sex, ethnicity/race, educational level, marital, and veteran status will be asked.

#### Health behavior covariates

Since poor health habits have been shown to cluster together [53-55] and our prior research has shown that problem drinking, greater body mass index (BMI) and greater physical activity levels predict use of sunscreen and/or sun burning [23], questions will be asked about other health behaviors including smoking (Heavy Smoking Index) [56], problem drinking (Alcohol Use Disorders Identification Test-Hepatitis C: AUDIT-C) [57], diet (two questions on fruit and vegetable intake from the validated Willett food frequency questionnaire) [58], a validated physical activity questionnaire [59], and Medical Outcomes Study sleep quality survey [60]. Self-reported height and weight will be used to determine BMI (weight in kilograms divided by the square of height in meters).

#### Job characteristic covariates

To determine if job characteristics impact sunscreen use and sun burning, several questions will be asked. Which type of work do you do (check all that apply): commercial, residential, heavy/civil, and road? What type of cab does the equipment you usually operate in the summer months have: Completely enclosed (i.e., windows, roof, and door); Partially enclosed (i.e., roof but no windows or door); Completely open (i.e., no roof, windows, or door)? How often do you operate heavy equipment during the summer months with the doors and/or windows of the cab open (More than 75% of the time; 50-75% of the time; 25-49% of the time; Less than 25% of the time)? Regional differences in sunscreen use and sun burning will be explored by the question: I am most likely to work in lower Michigan (below Saginaw, Midland and Muskegon), upper Michigan (above Saginaw, Midland and Muskegon, but not Upper Peninsula), Upper Peninsula, other (write in). Questions (yes/no) will be asked on whether they use other protective equipment including respirators, steel toed boots, high-visibility clothing, fall protection, hearing protection, safety glasses, hard hats, and work gloves. Standard industry (yes/no) questions will be asked on occupational exposures including asphalt fumes, heat stress, concrete dust, welding fumes, lead, benzene, asbestos, solvents, and silica [61].

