### Data analysis

Descriptive statistics will be computed for all variables at all measurement times. Distributions will be examined and variables will be transformed to normality if needed. The equivalence of the groups on pretest data will be tested using χ^2^ tests of association for categorical variables and Analysis of Variance (ANOVA) for continuous variables. Then analyses to meet the aim will be conducted by paired t-tests, RM-ANOVA, t-tests comparing change scores and by linear regression analyses. If the groups being compared in the RM-ANOVAs differ on the covariates, the analysis will be changed to repeated measures analysis of covariance (RM-ANCOVA) with the differing covariates controlled. Multiple imputation will be used to replace the values of missing data. An intent-to-treat approach will be used so that subjects are considered to be in the condition to which they were randomized despite how much they actually used that type of care. Analyses will be conducted by two-tailed tests with alpha of .05.

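### The cab-opening question has no unambiguous answer for operators whose usual cab has no windows or door, so some of the least sheltered can be coded as least exposed

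*Protocol article*

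**What the plan says.** The section on job characteristic covariates in the protocol article states its purpose: "To determine if job characteristics impact sunscreen use and sun burning, several questions will be asked". Two adjacent items there concern the cab.

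- **Cab type.** The question is "What type of cab does the equipment you usually operate in the summer months have". The answers are completely enclosed, "Partially enclosed (i.e., roof but no windows or door" and "Completely open (i.e., no roof, windows, or door", each of the last two with its closing bracket.
- **Cab opening.** The question is "How often do you operate heavy equipment during the summer months with the doors and/or windows of the cab open". The printed answers are "More than 75% of the time; 50-75% of the time; 25-49% of the time; Less than 25% of the time".

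The text gives no not-applicable answer, no filter by cab type and no rule for coding the two items together. Under Data analysis, a covariate enters the main model (RM-ANCOVA) only if the groups differ on it. On blanks the article says: "Multiple imputation will be used to replace the values of missing data".

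**The concern.** The second item presupposes doors or windows, and the first item defines two of its three categories as lacking both. For an operator in one of those categories, two opposite answers are reasonable. The cab is always open, so the answer is the band above 75%. Or there is nothing to open, so the answer is the band below 25%. The same physical exposure can therefore land at either end of the scale.

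This error is not spread evenly over respondents. It falls on the operators with the least shelter, and whenever it occurs it moves them from the most open end to the least open end. What is at stake is the stated purpose of these items, which is to learn whether job characteristics bear on sunscreen use and burning. An analysis of the opening item as ticked would understate the role of cab openness or miss it.

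**Working it through.** No figure in the article depends on this item, so there is none to reproduce. The sample size does not involve it: 64 per arm for an assumed standardised difference of 0.5 gives 4 × 64 = 256, and 256 / 0.80 = 320, as the article states.

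**The items side by side**

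| Usual cab | Windows or door? | Literal answer to the opening item |
|---|---|---|
| Completely enclosed | Yes | Any of the four bands, clear meaning |
| Partially enclosed | No (roof only) | Top band or bottom band, both defensible |
| Completely open | No | Top band or bottom band, both defensible |

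**How many could be affected.** The documents give neither the share *s* of operators in cabs without windows or door nor the share *q* of these who tick the bottom band. Both are assumptions here. The number miscoded among 256 completers is 256 × *s* × *q*:

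- *s* = 0.10 to 0.50 and *q* = 0 to 1 give 0 to 256 × 0.50 × 1 = 128.
- *s* = 0.30 and *q* = 0.5 give 256 × 0.30 × 0.5 = 38.4, about 38.

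**What it could do to the association.** The assumptions are:

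- True exposure X runs from 0 to 3. It is uniform over the four steps in enclosed cabs and equals 3 in the other two types.
- Burns rise by 0.30 per step.
- The coded answer W equals X in enclosed cabs. In the other types it is 0 with probability *q* and 3 otherwise.
- The opening item is analysed alone, as a linear score.

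Then

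- E[X] = 1.5(1 − s) + 3s
- E[W] = 1.5(1 − s) + 3s(1 − q)
- E[WX] = E[W²] = 3.5(1 − s) + 9s(1 − q)
- expected slope = 0.30 × (E[WX] − E[W]E[X]) / (E[W²] − E[W]²)

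Worked case, *s* = 0.40 and *q* = 0.5: E[X] = 2.1, E[W] = 1.5 and E[WX] = E[W²] = 3.9. The slope is 0.30 × (3.9 − 3.15) / (3.9 − 2.25) = 0.30 × 0.75 / 1.65 = 0.136.

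| Share *s* | All tick top band (*q* = 0) | Even split (*q* = 0.5) | All tick bottom band (*q* = 1) |
|---|---|---|---|
| 0.10 | 0.30 | 0.25 | 0.21 |
| 0.20 | 0.30 | 0.21 | 0.14 |
| 0.40 | 0.30 | 0.14 | 0.05 |
| 0.60 | 0.30 | 0.08 | -0.01 |

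Simulation with 320 subjects, residual SD 1.2 and 800 data sets per setting agrees to within 0.01. In the same simulation, leaving these answers blank and imputing them from a model that includes the outcome gave slopes of 0.30 to 0.31. Restricting the analysis to enclosed cabs gave 0.30.

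**The case against.** The other side has several good points, and most of them limit the concern rather than remove it.

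- **A reader might infer that these operators have no valid answer at all.** The text does not support that. The four bands cover the whole range from 0 to 100%, and the band above 75% is a natural and correctly placed answer for a cab that is always open. The defect is ambiguity. Nothing in the documents shows how many would choose the bottom band.
- **The two items have different frames.** Cab type refers to equipment usually operated, while the opening item refers to heavy equipment in general. Someone whose usual machine is open may also run enclosed ones and can then answer literally.
- **The damage is recoverable.** Cab type is recorded separately, so every affected respondent can be identified and recoded. Nothing in the article says the opening item will be analysed alone or as a linear score, and a coding rule may sit in an analysis plan that is not shown.
- **A reader might infer harm from imputation,** since it could assign a door-opening frequency to someone without doors. The simulated slope was about unchanged, so this is not a material problem.
- **A reader might infer that the trial's main comparison is at risk** through RM-ANCOVA. The item enters only if the arms differ on it, randomisation would be expected to spread the miscoding evenly over arms, and adjusting for a noisily measured baseline covariate does not bias a randomised contrast.
- **The article condenses the questionnaire.** A skip instruction may stand on the form.

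What survives is that the answer set as printed is ambiguous for two of the three cab types, and that the article states no rule to resolve it.

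**Conclusion.** The point holds as a minor one. As printed, the cab-opening item allows the same high exposure to be recorded at either end of its scale. If it is analysed as ticked, the association of cab openness with sunburn is attenuated. The size of that attenuation cannot be computed from the documents. The slopes from 0.25 down to -0.01 in the even-split and all-bottom columns rest on assumed shares of 10 to 60%, assumed answer patterns and a one-item linear analysis. The lowest values need 40 to 60% of operators in such cabs with all of them ticking the bottom band. If all tick the top band, nothing is lost.

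The consequence is confined to the exploratory question on job characteristics. The article's one specific aim, the difference in change among the four randomised arms, is essentially unaffected, as are the primary outcomes and the sample size.

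**What to change.** Add an answer to the opening item stating that the cab has no doors or windows, or ask the item only of operators who tick completely enclosed. If the questionnaire already does this, a phrase saying so is enough. If the survey is already in the field, use the recorded cab type to recode.

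In the analysis, treat the two items as one exposure variable: enclosed cabs graded by opening frequency, then partially enclosed, then completely open as separate, more exposed levels. The two types without windows or door should not be merged, because one has a roof and the other does not. State that an answer skipped by design is not applicable rather than missing.

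The cost is one answer option or one filter on the form and one coding line. The only downside is one or two more levels in an exploratory covariate.

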#### Additional evaluation questions

Evaluation questions (rated on a scale of strongly disagree to strongly agree) will vary depending on the intervention subjects received and will include: The educational presentation was easy to understand. The educational presentation and or mailed sunscreen and/or text message reminders were helpful. Overall I was satisfied with the presentation and or mailed sunscreen and/or text message reminders. I would recommend the sun protection intervention to others. A write in question will ask: What, if anything, would you change about the sun protection intervention?

### Data analysis

Descriptive statistics will be computed for all variables at all measurement times. Distributions will be examined and variables will be transformed to normality if needed. The equivalence of the groups on pretest data will be tested using χ^2^ tests of association for categorical variables and Analysis of Variance (ANOVA) for continuous variables. Then analyses to meet the aim will be conducted by paired t-tests, RM-ANOVA, t-tests comparing change scores and by linear regression analyses. If the groups being compared in the RM-ANOVAs differ on the covariates, the analysis will be changed to repeated measures analysis of covariance (RM-ANCOVA) with the differing covariates controlled. Multiple imputation will be used to replace the values of missing data. An intent-to-treat approach will be used so that subjects are considered to be in the condition to which they were randomized despite how much they actually used that type of care. Analyses will be conducted by two-tailed tests with alpha of .05.

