**Methods/design:**

Using the Health Belief Model as a guide, this randomized controlled trial (RCT) will test the efficacy of four sun protection interventions targeting Operating Engineers: a) education only; b) education and mailed sunscreen; c) education and text message reminders; and, d) education, mailed sunscreen, and text message reminders. Participations in the study will be offered during regularly scheduled safety trainings at the Local 324 Training Center. Pre- and post-intervention surveys will be collected to determine changes in sunscreen use and sun burning, the primary dependent variables. The analyses will include: a) paired t-tests to determine changes over time (from pre-intervention to post–intervention) in outcome variables (sunscreen use and burning) separately in the 4 intervention groups, b) Repeated Measures Analysis of Variance (RM-ANOVA) to compare the changes in outcomes across the 4 groups, and c) t-tests on change scores as follow-ups to the RM-ANOVA to determine exactly which groups differ from each other.

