#### Power analysis

Though limited research has been conducted on interventions to increase use of sunscreen among outdoor workers, a medium sized effect (as defined by Cohen) [28] is plausible based on the studies by Armstrong et al., Buller et al., and Stock et al. [29-31]. Power analysis conducted with PASS software [32] indicated a need for 256 subjects to have 80% power to detect medium sized effects on changes in sunscreen use and sunburn in tests comparing the four individual treatment groups both by tests for mean scores with alpha of .05 two tailed. This sample size will provide even more power for tests of the effects of the interventions over time (pre- versus post- intervention) separately in the four groups.

Based on our prior experience with this group, we expect to approach 460 Operating Engineers of which we expect 15% (n = 70) to be ineligible (e.g., no text messaging or cell phone) and 15% (n = 70) to refuse, allowing for 320 to be consented. Since some analyses will be conducted just on subjects with complete data, this sample size was adjusted to account for a 20% attrition rate found in our previous research on this population resulting in a final sample size of 256. This can easily be done as there are 16,000 Operating Engineers in Local 324 all of which will be eligible and our prior work has estimated that about 23% (3,680) are interested in sun protection interventions [23]. Note, however, that the main analysis will include all subjects following an intent-to-treat approach so will have a larger sample size and thus slightly higher power.

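### The single aim is tested by RM-ANOVA, change-score t-tests and a dummy-variable regression of equal standing, with no statement of which one decides

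*Protocol article*

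**What the plan says.** The protocol article states one specific aim, at the end of the Background: differences in changes in sunscreen use and sunburn among the four randomized groups. It describes the analysis for that aim in three places.

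- **Abstract, Methods/design.** Paired t-tests within groups, then RM-ANOVA across the four groups, then "t-tests on change scores as follow-ups to the RM-ANOVA to determine exactly which groups differ from each other". Regression is not mentioned.
- **Data analysis.** "Then analyses to meet the aim will be conducted by paired t-tests, RM-ANOVA, t-tests comparing change scores and by linear regression analyses". The order is gone and regression is added on the same footing. The section closes with "Analyses will be conducted by two-tailed tests with alpha of .05".
- **Independent variables.** Treatment enters as "3 dummy variables created from the four sun treatment conditions using the education only as the reference group". No other listed analysis needs a reference group, so this coding is naturally read as the regression's, although the article does not say so.

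The Power analysis section mentions a main analysis but identifies it only by its intent-to-treat population, not by its model.

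**The concern.** The abstract and the Data analysis section describe different plans for the same aim, and nothing says what follows when the analyses disagree. Each dummy coefficient carries its own test at .05, and none of them depends on the RM-ANOVA. A reader following the Data analysis section could declare mailed sunscreen, text messages or their combination better than education only from one significant dummy, although the overall comparison of the four groups was not significant. The Discussion intends to take the best interventions into a larger trial, so the choice of arm could depend on which table is read.

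**Working it through.** **Inputs from the article (Power analysis, Data analysis).** Four groups; two-sided alpha .05 for every test; a target of 256 analysed for 80% power at a medium effect, with the powered comparison described as "in tests comparing the four individual treatment groups both by tests for mean scores with alpha of .05 two tailed"; 20% attrition, hence 320 consented.

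**Assumed, because the article gives no figure.** Cohen's medium effect taken as d = 0.5; normal outcomes; pre-post correlation 0.3 to 0.7; correlation 0.5 between the two outcomes; a regression outcome that is either the change score or the post score adjusted for the pre score. Both regressions were run.

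**Step 1: the plan's own figure.** The normal approximation gives n = 2(1.960 + 0.842)² / 0.5² = 62.8, so 63 per group. The exact two-sample t-test gives 63.8, so 64 per group and 4 × 64 = 256 (power 80.1%). With 20% attrition, 256 / 0.80 = 320. Both figures reproduce. A four-group F-test at f = 0.25 would need only about 179 in total, so 256 corresponds to a pairwise t-test.

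**Step 2: the tests.** With two time points, the RM-ANOVA group-by-time test equals a one-way ANOVA on change scores: F = 64 × var(arm mean changes) / MSE on 3 and 252 df. A change-score dummy is tested by t = (mean change in arm j − mean change in education only) / √(2·MSE/64) on 252 df. The baseline-adjusted version regresses the post score on the pre score and the three dummies, with 256 − 5 = 251 df.

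**Step 3: no true effect, one outcome** (100,000 simulated trials, 64 per arm, pre-post correlation 0.5).

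| | Change-score regression | Baseline-adjusted regression |
|---|---|---|
| RM-ANOVA significant | 5.1% | 5.1% |
| At least one dummy significant | 12.5% | 12.6% |
| RM-ANOVA or any dummy significant | 13.5% | 14.4% |
| Dummy significant, RM-ANOVA not | 8.4% | 9.3% |

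For scale, three independent tests would give 1 − 0.95³ = 14.3%. The dummies share a reference arm, so the rate is somewhat lower.

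**Step 4: no true effect, both outcomes** (pre-post correlation 0.3 to 0.7).

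- RM-ANOVA alone: about 9–10%.
- Dummies alone: 20–24%.
- Either: 22–26%.
- A dummy significant on an outcome whose RM-ANOVA is not: 14–18%, across both regressions.
- Allowing both routes adds only about 1–4 points to the dummies alone, so most of the rise comes from the separate dummy tests.

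**Step 5: if the t-tests do not depend on the RM-ANOVA.** Six t-tests per outcome give 33–35% over both outcomes. Adding change-score dummies gives 34–36%, about 1 point more. Adding baseline-adjusted dummies gives 38–42%.

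**Step 6: disagreement on the same contrast when d = 0.5.** The change-score t-test and the dummy differ in significance in about 2% of trials with a change-score regression, and in 9–14% with a baseline-adjusted one.

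**Step 7: true change effects of 0, 0.25, 0.25 and 0.5 SD** (one outcome, pre-post correlation 0.5). RM-ANOVA power is 65%, while some dummy is significant in 83–91% of trials. In 19–27% of trials a dummy is significant and the RM-ANOVA is not.

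**The case against.** This is a journal article, and an analysis plan that is not shown may rank the methods. An abstract that leaves out one method is condensed rather than contradictory. The article never says that the t-tests run only after a significant RM-ANOVA, nor that one significant dummy would support an efficacy claim. On change scores without covariates, the regression's overall F-test is identical to the RM-ANOVA interaction test, and its three contrasts are a subset of the six pairwise ones.

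Much of this stands, and it rules out three stronger readings that a reader might infer:

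- *That the regression breaks a stated testing rule.* The word follow-ups implies a condition, but no rule is written. If there is none, uncorrected pairwise testing is the larger source of error and a change-score regression adds little to it.
- *That the routes give opposite answers.* They can differ in significant versus not significant. The documents give no ground for expecting effects in opposite directions.
- *That having two routes raises the error to about five times .05.* The 22–26% also reflects two outcomes and three uncorrected dummy tests. The second route itself accounts for a small part.

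The scope argument does not remove the point. The article does not merely leave detail out: it gives several analyses equal standing for one aim, each at .05, and states a differently ordered plan in its abstract.

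**Conclusion.** The concern holds in limited form. The article names no deciding analysis for its single aim, and its two descriptions of the analysis do not match. If the t-tests are read only after a significant RM-ANOVA, letting a dummy also decide raises the false-claim rate from about 5% to 13–14% per outcome, and from 9–10% to 22–26% over both. This holds for either regression and changes little across pre-post correlations of 0.3 to 0.7. If the t-tests are unconditional, the rate is already about 33–36% over both outcomes, and what the regression adds depends on its unstated outcome variable. The same-contrast disagreement of 9–14% applies only to a baseline-adjusted regression. All rates assume normal outcomes and 64 per arm. The sample size of 256 is not in question. Multiplicity across the two outcomes, and among the pairwise tests, is a separate matter.

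**What to change.** In Data analysis, name one deciding analysis per outcome. Concretely: regress the post score on the baseline score and the three arm dummies, let the joint 3-df arm test decide, and read individual contrasts only if it is significant. Label RM-ANOVA and the change-score t-tests as supportive, with no claim resting on them alone. This brings the rate for any false claim under no effect back to about 5% per outcome, about 10% over both.

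Alternatively, keep RM-ANOVA as the deciding test, state that follow-ups are read only after a significant result, and report the regression as estimates and confidence intervals without significance claims. In either case, align the abstract and the Independent variables section.

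The change needs no new subjects or data. Its cost is that a lone significant dummy after a non-significant overall test can no longer be claimed. The trial was sized for a pairwise contrast, so the power of an overall test depends on the pattern of effects: for RM-ANOVA at pre-post correlation 0.5 it is 84% if only one arm gains 0.5 SD, and 65% with gains of 0.25, 0.25 and 0.5 SD.
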